#### *Power calculation*

The sample size was calculated by taking published data as well as economic feasibility into account to allow the estimation of differences in the prevalence of type-specific HPV between the high-risk and control groups. From preliminary results obtained from the first 1300 women enrolled (717 SPSW, 290 HIVW, 160 RMW and 133 1326 G), the prevalence varied from 0.5%–2% (for major high-risk HPV genotypes: 16, 18, 31, 51, 52, 53) in the control group, and was 2–3 fold higher in the high-risk groups (for HPV 16, 31, 51, 52, 53). The planed sample of 1000 women for each high-risk group and 2000 low-risk women will be adequate to detect differences for genotypes with a prevalence of 1%–1.5% in the control group.

#### *Prospective study*

We will analyze the incidence of new cytological abnormalities, progression or regression of baseline lesions, incidence, clearance and persistence of HPV infection for all women who had at least one follow-up visit. The proportion of women lost to follow-up is expected to be different in each participant group. The RMW group may have more difficulty in returning for a follow-up visit. Socio-demographic differences between women who return and who are lost to follow-up will be analysed. Conversely, women in the HIV cohort, who will be recruited from the centre they attend for HIV treatment, may be more likely to attend the study follow-up visits.

The proportions of women who we expect to be lost to follow-up are therefore estimated at around 10%, 20% and 60% in the HIVW, SPSW and RMW groups, respectively.

Single and multiple infections will be defined without considering uncharacterized HPV types (HPV X). The Kaplan-Meier method will be used to evaluate differences in the incidence of abnormal cytology at follow-up between women in the high-risk groups versus the control group. When appropriate, a Cox model will be used to account for the effects of major confounding factors. For the paediatric group, we will recruit about 250 girls for each year of age between 13 and 18 years to estimate the age at first HPV infection, time to clearance or persistence of HPV infection, and the change after 3 years of follow-up related to major behavioural characteristics.

All the analyses will be performed using SAS software for Windows version 9.2 (SAS Institute Inc., Cary).

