### Baseline evaluation and follow-up

Adult participants will undergo a medical assessment appropriate to their group (gynaecologic evaluation, and infectious disease evaluation for HIV-infected participants), cytological screening following the Italian Guidelines [31] for Cervical Cancer or algorithms modified for HIV-infected women, and HPV DNA testing. Colposcopy referral will be driven by cytology results. The conventional Pap smears will be evaluated according to the 2001 Bethesda System by four pathology laboratories.

HPV-DNA testing will be performed by the reference virology laboratory. HPV DNA-positive samples will be genotyped using a commercial kit in the four microbiology laboratories. Oncogenic risk associated with HPV types will be defined according to the 2011 IARC classification [32]. Samples with a positive HPV DNA test but with genotypes not included in the InnoLipa panel will be typed by the restriction fragments length polymorphism (RFLP) technique in the reference virology laboratory. In this reference laboratory, HPV 16- and HPV 18-positive cervical brushes or urine samples will be further subjected to a phylogenetic analysis to study the circulation of variants belonging to different geographical clusters (European and non-European).

An additional analysis for the characterization of HPV 16 and HPV 18 variants that could potentially elude the immune response induced by the vaccination (escape mutants) will be performed.

Participants with discordant results (HPV-positive/cytology-negative) will be recalled after 12 months for reassessment with cytology and HPV testing.

Paediatric participants will undergo a paediatric evaluation and HPV DNA testing of urine samples. The algorithms for the follow-up of adult and paediatric participants are presented in Figure 1, Figure 2, Figure 3, and Figure 4. All data collected during the visits and derived from cytology and biomolecular evaluations will be recorded on a specially developed secure electronic case report form (eCRF).

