**Figure 1 F1:**
[figure not shown]
**Algorithm for the screening and follow-up of SPSW and RMW.** SPSW: women aged 26–65 years attending a gynaecologic visit for spontaneous screening. RMW: recently migrated women aged 26–65 years asking for medical assessment of any health problem. HPV testing: Nucleic acid extraction from cervical samples (by NucliSENS*®* EasyMAG™, bioMérieux bv, France) followed by PCR amplification of a 450-base pair fragment of ORF L1 using the degenerate primer pair ELSI-f and ELSI-r.

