**Figure 2 F2:**
[figure not shown]
**Algorithm for the screening and follow-up of HIVW.** HIVW: HIV-infected women aged 26–65 years. HPV testing: Nucleic acid extraction from cervical samples (by NucliSENS*®* EasyMAG™, bioMérieux bv, France) followed by PCR amplification of a 450-base pair fragment of ORF L1 using the degenerate primer pair ELSI-f and ELSI-r.

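### Cytology timing depends on baseline HPV result and, for HIV-infected women, on a different algorithm, so Kaplan-Meier and Cox comparisons can mix incidence with examination frequency

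*Protocol article*

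**What the plan says.** Under Prospective study, the article sets the between-group method: "The Kaplan-Meier method will be used to evaluate differences in the incidence of abnormal cytology at follow-up" in the high-risk groups versus the control group. A Cox model is added when appropriate, for major confounders. The analysis set is women with at least one follow-up visit. Expected loss is about 10% in HIV-infected women, 20% in controls and 60% in recent migrants. Regression of lesions is itself an outcome.

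Under Baseline evaluation and follow-up, examination depends on two things. One is the baseline HPV result: "Participants with discordant results (HPV-positive/cytology-negative) will be recalled after 12 months for reassessment with cytology and HPV testing". The other is the group: "cytological screening following the Italian Guidelines [31] for Cervical Cancer or algorithms modified for HIV-infected women". The intervals are left to diagrams: "The algorithms for the follow-up of adult and paediatric participants are presented in Figure 1, Figure 2, Figure 3, and Figure 4". Their captions show one diagram shared by controls and migrants ("Algorithm for the screening and follow-up of SPSW and RMW"), a separate one for HIV-infected women ("Algorithm for the screening and follow-up of HIVW"), and another for young women seen in gynaecology.

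Under Power calculation, type-specific prevalence in the first 1300 women was 0.5%–2% in controls "and was 2–3 fold higher in the high-risk groups (for HPV 16, 31, 51, 52, 53").

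**The concern.** The onset of abnormal cytology is not observed. It is known only to lie between the last normal smear and the first abnormal one, and an abnormality that regresses between smears is never seen. Ordinary Kaplan-Meier and Cox analyses need one event date, and with visit data that is naturally the detecting visit. Two groups with the same true incidence but different smear frequency then give different curves and can give a hazard ratio other than 1. Adjusting for confounders does not remove a difference in schedule.

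This is the only between-group time-to-event comparison of abnormal cytology that the Prospective study section names, and the results are meant to guide regional prevention. Part of an excess seen in a more closely examined group could be an effect of surveillance.

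**Working it through.** The article gives no event count, power or effect size for this comparison, so there is no figure to reproduce. The check asks what the named methods return when the true hazard ratio is exactly 1.

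**From the article.** Follow-up 3 years; loss 20% (controls) and 10% (HIV-infected women); only women with at least one follow-up visit; 12-month recall if HPV-positive/cytology-negative.

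**Assumed.** Onset rate λ = 0.03 per year in both groups, independent of HPV status. Regression rate μ = 0, 0.5 or 1.0 per year. HPV-positive 15% of controls and 40% of HIV-infected women (ratio 2.7). Visit intervals as listed below.

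**Closed form.** A woman normal at one visit is abnormal at a visit d years later with probability

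p(d) = λ/(λ+μ) × [1 − exp(−(λ+μ)d)].

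With μ = 1.0:
- p(1) = 0.0291 × (1 − e^−1.03) = 0.0187 and p(3) = 0.0291 × (1 − e^−3.09) = 0.0278.
- Yearly visits, detected by 3 years: 1 − (1 − 0.0187)³ = 0.0551. One visit at 36 months: 0.0278.
- Controls (HPV-positive yearly, HPV-negative at 36 months only): 0.15 × 0.0551 + 0.85 × 0.0278 = 0.0319.
- Ratio of cumulative hazards if all HIV-infected women are seen yearly: ln(1 − 0.0551)/ln(1 − 0.0319) = 1.75.
- Same HPV-driven rule in both groups: 0.40 × 0.0551 + 0.60 × 0.0278 = 0.0387, ratio 1.22.

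With μ = 0, all schedules detect 1 − e^−0.09 = 8.6% by 3 years, so the ratio is 1.00. The 12-month curves still differ: 0.15 × 2.96% = 0.4% in controls against 2.96% with yearly visits.

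**Simulation.** 20,000 women per group, event dated at the detecting visit, Cox with Efron ties, standard error of the log hazard ratio 0.036–0.059. Closed-form ratio in brackets.

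| Schedule | μ = 0 | μ = 0.5 | μ = 1.0 |
|---|---|---|---|
| Both groups yearly | 0.97 (1.00) | 0.97 (1.00) | 0.99 (1.00) |
| 1. Controls HPV-negative 36 months, HPV-positive yearly; HIV-infected yearly | 1.07 (1.00) | 1.42 (1.42) | 1.71 (1.75) |
| 2. Controls as in 1; HIV-infected 6-monthly | 1.06 (1.00) | 1.75 (1.60) | 2.16 (2.18) |
| 3. Same HPV-driven rule in both groups (HPV-negative 36 months, HPV-positive yearly) | 0.98 (1.00) | 1.06 (1.12) | 1.22 (1.22) |
| 4. As 3, HPV-positive at 12 and 36 months only | 0.97 (1.00) | 1.07 (1.08) | 1.14 (1.13) |
| 5. Controls yearly; HIV-infected 6-monthly | 1.06 (1.00) | 1.15 (1.13) | 1.33 (1.25) |

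In schedule 1 with μ = 0, simulated Kaplan-Meier incidence is 0.4% v 2.9% at 12 months, 0.9% v 5.8% at 24 months, and 8.7% v 8.9% at 36 months.

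**Recent migrants.** They share the controls' algorithm, so planned timing differs only through HPV status. Treating the expected loss as visits missed at random (60% v 20%, an assumption), with λ = 0.03, a shared yearly schedule gives hazard ratios of 1.09, 0.91 and 0.86 at μ = 0, 0.5 and 1.0. The shared HPV-driven rule (15% v 40% positive) gives 1.19, 1.13 and 1.24. The bias can go either way.

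**Does interval censoring alone suffice?** Fitting a constant interval-censored hazard to schedule 1 gives 0.0300 v 0.0300 per year at μ = 0, which restores the timing. At μ = 0.5 it gives 0.0236/0.0166 = 1.42 and at μ = 1.0 it gives 0.0189/0.0108 = 1.75, as before. It places events correctly in time but cannot recover abnormalities that nobody saw.

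**The case against.** The strongest reply is that the intervals are in figures not shown. The words "or algorithms modified for HIV-infected women" do not say more frequent, and nowhere does the text say that controls are seen mainly at 36 months. This stands. A reader might infer that high-risk women are examined more often by design; the text supports only that timing differs by HPV result and that HIV-infected women have their own algorithm. The hazard ratios of 1.4–2.2 need the assumed contrast in schedules 1 and 2. The stated recall rule alone gives at most about 1.2.

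Other stronger readings also fail:
- A bias away from 1 in every high-risk group: migrants share the controls' algorithm and have 60% expected loss, so the direction there is open.
- A 2–3 fold larger share under recall: that ratio is for five individual genotypes, whereas recall follows overall HPV positivity, for which no group figures are given.
- Damage to the main prospective result: no main prospective endpoint is named, and the cohort's stated aim is to compare Pap with HPV testing.
- The same fault in age at first HPV infection among girls: no estimator is stated for it, so nothing is fixed wrongly.

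It may also be said that event dating belongs in an analysis plan. Silence on it is indeed no finding. The point rests on the two methods that the article names; in their ordinary form they do not allow for visit-dependent detection.

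Finally, replacing the endpoint with cytology at 36 months alone would bring its own bias, because cytology showing atypical squamous cells or worse leads to colposcopy referral. If every interim abnormality were resolved by then and counted as event-free (an extreme case), the 36-month risk ratio in schedule 1 would be 0.0278/0.0773 = 0.36 at μ = 0 and 0.0180/0.0263 = 0.68 at μ = 1.0. This stands, and it is why the common-time comparison below is a sensitivity analysis with an explicit rule.

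**Conclusion.** The concern holds conditionally. As named, Kaplan-Meier and Cox can mix incidence of abnormal cytology with examination frequency, chiefly for groups whose algorithm differs from the controls'. That is clearest for HIV-infected women; young women seen in gynaecology also have their own algorithm, but it was not modelled. With equal true incidence:
- abnormalities that persist: hazard ratio about 1.0–1.1, but early separation of the curves from timing alone;
- only the shared HPV-driven recall: up to about 1.2;
- HIV-infected women seen more often and abnormalities regressing: about 1.4–2.2 if HPV-negative controls are seen only at 36 months, and about 1.15–1.33 if controls are seen yearly and HIV-infected women 6-monthly;
- recent migrants: direction uncertain.

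These sizes rest on the assumed visit intervals, regression rates, onset rate and HPV positivity. The mechanism rests on the article's own text.

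**What to change.** Amend the Prospective study text as follows.
- **Main analysis:** in women cytology-negative at baseline, analyse time to abnormal cytology as interval-censored data, or by a discrete-time complementary log-log model with log interval length as offset, instead of dating the event at the visit.
- **Sensitivity analysis (a):** compare groups using only assessment times common to both, including about 3 years. State a rule for women already found abnormal or treated at an interim visit, and do not count them as event-free; for example, count them as events in one version and show them as a separate outcome category in another. The first version brings back some of the detection difference, so both are needed.
- **Sensitivity analysis (b):** stratify by baseline HPV result, so that women under the same recall rule are compared. HPV status may lie on the pathway from group to abnormality, so this answers a narrower question.
- **Reporting:** give the number and timing of cytology examinations by group and baseline HPV result.

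No visit, test or schedule changes. The cost is slightly more analysis work and wider intervals. Interval censoring alone does not remove bias from missed transient abnormalities, so analysis (a) is not optional.

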## Discussion/Main expected results and impact

In the last 50 years, the introduction of screening methods has substantially reduced the incidence of cervical cancer in the industrialised world. However, inequalities in the distribution of cervical cancer prevalence and mortality are still present at national, regional or local levels. In general, high-risk women are those who are not reached for any reason by prevention and screening programs. This study will provide substantial insight on HPV infections and related cervical diseases, which will enable us to define the risk of cervical cancer and its precursor lesions in high-risk women compared with the general population living in the Lombardy Region. In turn, this information will assist health care providers and policy makers to improve regional strategies and optimize cervical cancer prevention in high-risk groups.

## Abbreviations

VALHIDATE: eVALuation and monitoring of HPV Infections and relATEd cervical diseases in high-risk women; CIN: Cervical Intraepithelial Neoplasia; SPsW: Spontaneous Pap Screening Program Women; HIVW: HIV infected women; RMW: Recent Migrant Women; 1326G: women aged 13–26 referred to gynaecologic consultation; 1326P: women aged 13–26 referred to paediatric consultation; RFLP: Restriction Fragment Length Polymorphism; eCRF: electronic Case Report Form; RT: Room Temperature; PBS: Phosphate Buffered Saline.

## Study protocol

Sacco Hospital Ethical Committee resolution n35 (3^rd^ Feb 2010), Sacco Hosp General Direction Resolution n174/2010 (9 March 2010).
